### Ethical considerations

The trial protocol has been approved by the Danish Data Protection Agency as well as the regional ethics committee (registration number H-2-2011-007). All data gathered will be coded in order to secure anonymity of the patient. Data are filed in secure drives and servers, and if physical i.e. questionnaires data, stored in secured archives thus only accessible to the investigator.

### Risk/benefits

The intervention of the trial is non-pharmaceutical thus potential risks relate to eventual wrongly given information and advise about skin care and skin protection. It is expected that misinformation will be hypothetical. The patients in the intervention group are expected to gain from the Healthy Skin Clinic in a way that makes them more knowledgeable and confident of their eczematous disease.

At present in Denmark, no standards or guidelines as to information and guidance to patients with chronic hand eczema exist. The patients in the control group will receive conventional information, i.e. written information sheets, in relation to medical consultations and allergy tests. Hence, they are not deprived from any usual care. By the end of the trial, participants in the control group are offered counselling given analogous to the Healthy Skin Clinic.

### Informed consent

By giving the signed, informed consent, participants accept to be informed of 1) the aim of the trial, 2) the voluntariness of their participation, 3) the fact that no consequences to the individual will occur as to continuous treatment if they choose to withdraw their consent, and 4) that all data concerning their health and daily life is to be used only with anonymity.

### Trial conduct

The trial will be conducted in compliance with the protocol, and no deviations from the protocol will be implemented without the prior review and approval of the regulatory authorities i.e. the Danish Data Protection Agency and the regional ethics committee.

### Blinding

The trial complies with usual clinical practice and the involved health professional actors will be the investigator and the members of the intervention team. It has been judged not to be feasible to maintain a fully blinded design throughout the trial. An effort is made to prevent performance bias by making the HECSI-scoring prior to randomisation. The HECSI scores are then removed from the participants’ data file to make the outcome assessment as blinded as possible. Also, when measuring primary outcome at six months follow-up, attempts are made to randomly allocate the member of the team, who does the HECSI-scoring. Hence, the participant may have been included by one member of the team; have been counselled by another; and have had final outcome assessed by a third member of the intervention team.

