### Primary outcome

#### Objective severity of hand eczema

The primary outcome variable is the change from baseline (T_0_) to follow up in objectively assessed disease severity, which is evaluated clinically by a member of the intervention team. The assessment relies on the Hand Eczema Severity Index (HECSI) which is a validated scoring system developed to quantify severity of hand eczema. HECSI is a visual medical assessment and subjective symptoms of the patient, e.g. itch or pain are not included 
[31]. Inter-rater variability in the present trial will be evaluated by random checks where patients are scored twice independently and by different assessors.

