### Statistical plan and data analysis sample size estimation

Studies examining patient compliance by the use of intervention group and group of control patients are usually recommended to include a minimum of 60 participants in each group if an absolute difference in effect of 25% between groups is to be demonstrated at a probability of 80% 
[14]. Medication adherence is not easily measured in particular when it comes to dynamic conditions like eczema with treatment being a combination of a topical pharmaceutical and preventive behaviour 
[43]. Also, power calculation is hampered by uncertainty of whether an individual action plan may promote a clinically improvement when under the influence of exogenous factors related to the patient. In a previous study that used HECSI-score as outcome variable an average score of 11.2 was detected at six months follow-up compared to an average score of 19.9 at baseline (n = 366) 
[44]. With reference to this follow-up score in the control group and assuming an improvement of 30% due to the intervention, a power calculation carry out a sample size need of at least 87 patients in each group. In details, the sample size is calculated based upon the following values at six months follow-up along with estimated standard deviations: Control group mean-HECSI 11 (SD 9.0) and Intervention group mean-HECSI 7.7 (SD 6.0). Applying an alpha error level at 5%; and a beta error level at 90%, the use of 2-samples average data input bring forward a need of 87 participants in each group to detect a difference (http:/www.ddsresearch.com/toolkit/sscalc/size_a2.asp).

With a 15% excess of the number due to non-parametric variables and with caution due to the heterogeneities of the sample, and to the probability of dropouts, it has been assessed that inclusion of 150 patients in each group may be sufficient to show the anticipated effect of the intervention in question. No studies with estimated sample sizes based on ‘the minimal clinically importan difference’ of life quality measures have been identified. However, when using SF-36 as efficacy variable a minimum of 71 patients in each group are requested in order to demonstrate an achieved effect size of 0.5 
[45]. Others propose a minimum of 80 in each group in interventional studies, targeting changes in health behaviour 
[46]. Hence, both figures are within the range of the present estimated sample size.

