### Statistical methods

All data obtained at baseline will be given a coded ID-number before they are used in further statistical analyses. After double data entry and with the guidance of a statistician, statistical analysis will be performed in SPSS. Stratification for relevant confounders will be performed and descriptive statistics as well as multivariate analyses will be conducted. Ordinal scaled data will be evaluated as to a Gaussian distribution after which between-group differences will be tested in accordance by the use of *t*-test or non-parametric test. Dichotomous efficacy variables are tested by use of chi^2^ test or exact test in case of small numbers. The significance level will be a p-value of less than 0.05.

The final number of patients included in the trial will be reported and intention-to-treat analyses are to be performed meaning all participants will be included in the analysis irrespective of compliance with the intervention protocol. However, an additional per-protocol analysis will also be conducted. Data from patients who refused to participate, dropouts, and loss-to-follow-up participants will be entered to an analysis based upon demographics in order to consider selection bias when interpreting the results. The presentation of the trial results will be according to the CONSORT statement to Trials of Nonpharmacologic Treatment 
[47].

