## Discussion

In this paper the protocol of a large randomised controlled trial in the clinical field of Dermatology is presented. The trial aims at evaluating a newly developed guidance programme which is expected to support self-management of patients referred to dermatology treatment due to chronic hand eczema. The design of the protocol is pragmatic and data analysis will be conducted with blinding of neither participants nor the investigator. Thus, potential observer bias may be a risk in the interpretation of the results. However, allocation to the two arms in the trial i.e. the intervention group and the control group is done by randomisation performed after the baseline assessment of the primary outcome variable. Other efforts are done in order to increase rigor of the trial. In the follow-up assessment of outcome variables, attempts are made ‘to be oblivious of’ the severity scores at baseline by deliberate removal of these sheets from the data files. Furthermore, the randomness inherent in the process of being a team of assessors both at baseline and at follow-up may prevent observer bias.

Finally, in the interpretation of the results, the investigator takes into account effects that may be attributed to actors of the interventions rather than the intervention per se 
[47,48].

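### HECSI scores at baseline and six months may come from different assessors, and the named between-group test ignores assessor: an avoidable, probably modest loss of precision, not a bias

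*Protocol article*

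**What the plan says.** The section Objective severity of hand eczema defines the outcome: "The primary outcome variable is the change from baseline (T_0_) to follow up in objectively assessed disease severity". The score is a visual assessment made by a member of the intervention team. The same section adds a reliability check: "Inter-rater variability in the present trial will be evaluated by random checks where patients are scored twice independently and by different assessors". It does not say how the result of that check is used.

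The Blinding section describes who scores at six months: "attempts are made to randomly allocate the member of the team, who does the HECSI-scoring". It then gives the possible consequence that a participant is included by one member, counselled by another, and may "have had final outcome assessed by a third member of the intervention team". The Discussion presents this as a safeguard: "the randomness inherent in the process of being a team of assessors both at baseline and at follow-up may prevent observer bias".

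Under Statistical methods, "between-group differences will be tested in accordance by the use of *t*-test or non-parametric test". The same section also announces that "Stratification for relevant confounders will be performed and descriptive statistics as well as multivariate analyses will be conducted", without listing covariates and without tying these analyses to the primary outcome or to assessors.

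**The concern.** When two people score the two visits, the recorded change is the true change plus the follow-up assessor's leniency minus the baseline assessor's leniency. Drawing assessors at random breaks any systematic link between assessor and arm. It does not remove the differences between assessors; it turns them into noise. The Discussion credits the team arrangement with preventing observer bias but does not mention this cost, and the named test has no means of recovering it.

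Precision in the primary comparison is at stake. A second, conditional issue is that the draw is described only as an attempt. If it failed in a way related to arm, assessor differences would enter the treatment effect directly. This point is separate from whether the assessor knows the patient's arm.

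**Working it through.** **Inputs from the protocol article** (sample size section): six-month means 11 and 7.7, so a difference of 3.3; SDs 9.0 and 6.0; alpha 5%; what is called a beta error level of 90%, read here as 90% power; 150 per group.

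**Not in the article, so assumed:** the between-assessor SD (s), the SD of change, and two-sided testing.

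**The plan's own figure.** n per group = (9.0² + 6.0²)(z_alpha + z_power)² / 3.3². For two-sided 5% and 90% power: 117 × (1.960 + 1.282)² / 10.89 = 112.9, so 113. One-sided gives 93. Two-sided at 80% power gives 85. The stated 87 is therefore not reproduced at 90% power and is closest to 80%. That is a separate matter. It affects this point only because the calculation uses follow-up scores and shows no explicit term for assessor variance.

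**Effect of assessor variance.** With independently drawn assessors, each change gains variance 2s², so the sum over the two arms gains 4s²:

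- V = SD1² + SD2² + 4s²
- power = Φ(3.3 / √(V/150) − 1.96)

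Example for SDs 9.0 and 6.0 with s = 3: V = 117 + 36 = 153; √(153/150) = 1.010; 3.3/1.010 − 1.96 = 1.31; power 90.4%.

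| Assessor SD s (assumed) | SD of change 9.0 and 6.0, 150 per arm | Same SDs, 127 analysed per arm (assumed 15% loss) | SD of change 9 in both arms, 150 per arm |
|---|---|---|---|
| 0 | 96.2% | 93.0% | 88.8% |
| 2 | 93.9% | 89.7% | 85.8% |
| 3 | 90.4% | 85.2% | 81.9% |
| 4 | 85.2% | 78.9% | 76.7% |

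**The SD of change matters more.** With an assumed baseline SD of 12 and correlation 0.5, the change variances are 144 + 81 − 108 = 117 (control) and 144 + 36 − 72 = 108 (intervention). Power at 150 per arm is then 77% with no assessor variance at all, and 74%, 71% and 66% at s = 2, 3 and 4.

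**Bias and type I error.** In a simulation (150 per arm, five assessors drawn at random, 1,500 runs per setting), the unadjusted comparison gave type I error of 5.3% at both s = 2 and s = 4. Mean estimates were −3.26 and −3.31 against a true −3.3, and power was 93.5% and 88.5%. Adding baseline and follow-up assessor terms brought power to 96–97%, with type I error of 4.8% and 5.2%.

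The simulated 88.5% at s = 4 is milder than the formula's 85.2%. With five assessors, one patient in five gets the same assessor twice, and for that patient the stable difference cancels. The added variance is then 4 × 16 × 4/5 = 51.2, V = 168.2, and power is about 88%.

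**If the draw fails.** Bias = assessor difference × imbalance in share. With an assumed gap of 3 points between two assessors and a 20 to 30 percentage-point difference in their share between arms, bias is 0.6 to 0.9 points, or 18% to 27% of 3.3. By chance alone, the SE of that share difference is √(0.25 × 2/150) = 5.8 percentage points. An imbalance of 20 to 30 points is therefore about 3.5 to 5.2 SE and would need a systematic failure of the draw.

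**The case against.** Three stronger readings are tempting, and the article supports none of them.

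- **That different assessors are certain.** The text says a participant may meet different members and that allocation is attempted. The same person at both visits is not excluded, and within one setting's small team it will happen often. Each such case removes the stable assessor difference from that patient's change.
- **That an assessor term is ruled out.** Multivariate analyses are planned with unlisted covariates, and a condensed article commonly leaves such lists to a fuller document. Silence is no defect in itself. What remains is that the one between-group test actually named cannot account for assessor.
- **That the treatment effect is biased.** Baseline scoring precedes randomisation, randomisation is stratified by setting, and a random follow-up draw is neutral between arms. The simulation shows no bias. The 0.6 to 0.9 point figure needs a breakdown of the draw that nothing in the article shows. The only textual opening is that the draw is described as an attempt.

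The size of the loss is also open to challenge. No assessor SD is given, and 4 points would be 36% to 52% of the expected means of 11 and 7.7. The stated SDs describe observed scores and may already contain rater error, so adding it again may double-count. A rank test does not follow the variance formula exactly. All of this stands: it limits the magnitude but not the direction.

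Finally, the random draw is a deliberate guard against observer bias, and requiring one assessor per patient would weaken it. That is right, and the remedy here leaves the draw in place.

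**Conclusion.** The concern holds as a point about precision. The primary change may combine scores from two assessors, the named test does not account for this, and stable assessor differences therefore add variance that could be recovered at almost no cost.

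The size cannot be fixed from the article. If the SD of change equals 9.0 and 6.0, with 150 analysed per arm and two-sided 5%, an assessor SD of 2 to 4 points takes about 2 to 11 percentage points off a power of 96%. With an SD of 9 in both arms, it takes about 3 to 12 points off 89%. Up to an assessor SD of 3, the first scenario stays at or above 90%.

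With a working random draw there is no bias and the type I error is kept. Minor priority: this improves precision and is not an error that would invalidate the result.

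**What to change.** - Keep the random draw of assessors at six months.
- Record an assessor code with every HECSI score at both visits. If it is not captured when the score is taken, it may not be recoverable later.
- Analyse HECSI in a model with treatment arm, baseline assessor and follow-up assessor as factors, using random effects if there are many assessors. The baseline factor is fixed before randomisation and the follow-up factor is meant to be drawn at random, so neither should distort the treatment comparison.
- Report the assessor-by-arm table, so that readers can see whether the draw worked.
- State the inter-rater SD from the planned double scoring beside the treatment estimate.

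The cost is one code per score form, two model terms and a few degrees of freedom. In the simulation the adjustment brought power back to the level expected without assessor differences.

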### Trial intervention

The trial aims at intervening multi modally through initiatives which separately may be expected to support patient self-management and to be beneficial to the hand eczema prognosis 
[10,13,15,27-29]. The intervention is named The Healthy Skin Clinic in order to emphasise that self-management of hand eczema is more than medication adherence thus also involves health promotion. The Healthy Skin Clinic complies with usual clinical practice aiming to provide the patient with a systematic, yet individually, based counselling programme including a support module. The Healthy Skin Clinic is maintained by experienced nurses within the dermatological specialty along with the investigator (setting A), or by an experienced health care assistant supervised by the investigator and a dermatologist (setting B). A high level of team communication is conducted in order to provide commonality of the intervention.

The intervention is founded upon three concurrent elements. Firstly, a SKIN-profile is generated by responses from the baseline questionnaire. The profile is descriptive of the patient regarding susceptibility; knowledge; co-morbidity; social support; and necessary precautions i.e. allergies and aggravating irritant factors. One significant purpose of generating the profile is to clarify the multifactorial aetiology of (the persistence of) chronic hand eczema thus direct focus to the relevant areas in the following nurse-led consultation.

Secondly, a patient self-management book is offered. The book is a dynamic tool, which is launched in an electronic form, i.e. a secure website. Patients, with no possibilities of using information technology, will be handed over a physical book containing the same features. The patient self-management book contains information material which is tailored to the SKIN-profile. In addition, tools for self-monitoring of the disease are offered with the purpose of encouraging the patient to take a more proactive role in the course.

Finally, in addition to the nurse-led consultation, support to self-management through asynchronous communication and networking is offered. The online users may facilitate contact to either the intervention team or to other trial participants by use of the website. To the users of the physical self-management book a telephone based hotline is offered. An overall graphical depiction of the Healthy Skin Clinic intervention is presented in Figure 

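### The six-month HECSI is scored within the intervention team with no stated rule that separates assessor from counsellor or masks the arm, and the stated safeguards are given too much credit

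*Protocol article*

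**What the plan says.** The primary outcome is the change in HECSI from baseline to six months, "which is evaluated clinically by a member of the intervention team" (Primary outcome, Objective severity of hand eczema). The same section describes HECSI as a visual assessment and plans random double scoring to study inter-rater variability.

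The Blinding section states: "It has been judged not to be feasible to maintain a fully blinded design throughout the trial". It describes three measures:

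- Baseline HECSI is scored before randomisation.
- The baseline scores are taken out of the participant's file "to make the outcome assessment as blinded as possible".
- At six months, "attempts are made to randomly allocate the member of the team, who does the HECSI-scoring". As a result, a participant enrolled by one member may "have been counselled by another; and have had final outcome assessed by a third member of the intervention team".

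The Discussion repeats that "attempts are made ‘to be oblivious of’ the severity scores at baseline by deliberate removal of these sheets from the data files" and adds that "the randomness inherent in the process of being a team of assessors both at baseline and at follow-up may prevent observer bias". The Abstract and the Discussion both acknowledge potential observer bias.

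On staffing, the Trial intervention section says that the programme is run at setting A by nurses together with the investigator, and at setting B "by an experienced health care assistant supervised by the investigator and a dermatologist (setting B"). It gives no team sizes.

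**The concern.** The people who score the primary outcome come from the group that delivers the programme, and participants are not blinded. In such a design, detection bias at follow-up is kept in check only if the assessor does not know the arm, or at least did not counsel the participant. The article states neither as a requirement. Its wording on separate roles describes something that may happen, and random choice of assessor is only attempted.

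HECSI was made the primary outcome because it is the objectively assessed measure; the quality-of-life outcomes are self-reported by unblinded participants. A difference in scoring by arm would pass straight into the primary contrast. It could not be corrected afterwards, and the article describes no record of who scored or whether they knew the arm.

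**Working it through.** **Part 1: what each stated safeguard covers.**

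- *Scoring before randomisation.* It protects the baseline half of the change score. The six-month half stays exposed.
- *Removing the baseline sheets.* It stops the first score from anchoring the second, which is useful for a change score. It tells the assessor nothing less about the arm.
- *Random choice of assessor within the team.* It spreads differences between raters over both arms. It does not remove a bias shared by raters who know the arm, and it does not exclude the participant's own counsellor.
- *Random double scoring.* It measures disagreement. Two unmasked raters can agree and share the same bias.

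Only intervention participants receive the counselling, so an assessor who recognises someone from counselling knows the arm. The Trial intervention section also describes close communication within the team, so a member who did not counsel the participant may know it too.

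**Part 2: how much a scoring shift could matter.** The article gives no figure for scoring bias, so there is none to reproduce. What follows is an illustration.

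Inputs from the sample size section: control mean 11, SD 9.0, intervention mean 7.7, SD 6.0, 150 per group. Assumptions: no true effect, mean 11 and SD 9 in both arms, no dropout, a two-sided 5% test (critical value 1.96), and under-scoring of 5% or 10% in the intervention arm.

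Standard error of the difference: SE = √(2 × 9²/150) = √1.08 = 1.039.

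False favourable rate for a mean shift b: P(Z > 1.96 − b/SE).

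- No shift: P(Z > 1.96) = 2.5%.
- All intervention participants, 10% (b = 1.1): b/SE = 1.06; P(Z > 0.90) = 18%.
- All intervention participants, 5% (b = 0.55): b/SE = 0.53; P(Z > 1.43) = 7.6%.
- 10%, but only one in three affected (b = 1.1/3 = 0.37): b/SE = 0.35; P(Z > 1.61) = 5.4%.
- 10%, but only one in five affected (b = 1.1/5 = 0.22): b/SE = 0.21; P(Z > 1.75) = 4.0%.

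The one-in-three and one-in-five cases correspond to an assessor drawn at random from three or five people, one of whom was the counsellor, with only that person's scores biased. Team size is not stated.

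Two further checks:

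- With both stated SDs, SE = √((81 + 36)/150) = 0.883. A mean shift of 1.0 point then gives a two-sided type I error of about 20%.
- A larger sample does not help. At 87 per group, SE = √(2 × 81/87) = 1.365, and b = 1.1 gives P(Z > 1.15) = 12%, against 18% at 150 per group.

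For scale, 1.1 points is one third of the 3.3-point difference (11 − 7.7) that the trial is sized to detect.

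**The case against.** The strongest reply is that this is a disclosed limitation of a pragmatic open trial. The Abstract and the Discussion name potential observer bias, the Blinding section says that full blinding was judged infeasible, and the Discussion sentence on randomness is hedged. All of that stands, so the point is not that the article hides the weakness. But infeasibility of a fully blinded design does not explain why there is no rule on who scores. Nor can an unmeasured bias be corrected at interpretation.

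A reader might infer that the article claims sheet removal conceals allocation. It does not: it says that removal keeps assessors unaware of the baseline scores and serves blinding as far as possible. The fault is over-crediting.

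A reader might also infer that in setting B the counsellor will usually score their own participants. The article says who runs the programme there, not who scores or how often, so this is possible but not established.

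The magnitude is open to challenge as well. The 18% applies an assumed bias to every intervention participant. The calculation uses the SD of follow-up scores although the outcome is a change, and it ignores dropout.

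Finally, a rule that merely bars counsellors from scoring those they counselled would act on the intervention arm only, and so could tie rater to arm. Dropping own-counsellor scores from an analysis would be a one-arm exclusion after randomisation. Both objections are sound and shape the fix.

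Detailed rota and file-handling rules may sit in the full protocol, which is not shown. The point therefore rests on the procedure the article states and the protection it claims for it.

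**Conclusion.** The concern holds in this form: as described, the six-month primary outcome may be scored by an unmasked team member, including the participant's own counsellor, and none of the stated measures addresses knowledge of the arm. The Discussion's suggestion that the randomness of assessors could avert observer bias is not supported by the procedure.

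The size of any bias is unknown. Under the assumptions shown, the false favourable rate rises from 2.5% to about 18% if all intervention participants are scored 10% too low, and to about 5% if one in three is. These figures show sensitivity. They do not estimate the trial's error rate, and 18% should not be read as the expected value.

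**What to change.** Use existing staff and apply every step identically in both arms.

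1. Designate each participant's six-month assessor before randomisation, and do not let that person counsel the participant. Because the choice precedes allocation, it cannot tie rater to arm.
2. Where one person does the counselling, as setting B appears to be described, have another existing team member score both arms there.
3. Remove allocation and counselling notes, as well as the baseline HECSI, from the file given to the assessor. Score before any discussion, and ask participants beforehand not to mention the programme.
4. Record the assessor's identity and whether allocation was known, and report both by arm.
5. Include assessor in a sensitivity analysis. Do not exclude own-counsellor scores.
6. Replace the Discussion sentence on randomness with a statement that these steps reduce observer bias but do not remove it.

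The cost is a rota rule, a file-handling rule and two recorded items. The price is less freedom in scheduling visits and counselling, felt most where the team is small. Some unmasking will remain, since supervisors and colleagues may know the arm and participants may reveal it. The record in step 4 makes that visible.
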